#### Criteria for discontinuing or modifying allocated interventions {11b}

Patients who would develop severe complications from their SB (e.g., implant infection or intractable pain) which would require removal of the SB could undergo a second operation to remove it. Should the patient require silicon oil as a tamponade agent as deemed by the treating surgeon upon starting the operation (e.g., in cases of extensive PVR undetected preoperatively), the patient could therefore be removed from the study and treated accordingly.

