## Introduction

### Background and rationale {6a}

Two important and common techniques used in the surgical repair of rhegmatogenous retinal detachment (RRD) are pars plana vitrectomy (PPV) and scleral buckle (SB). Both can be used alone or in combination with a gradual shift towards PPV with improvements in technology and technique. Prominent retrospective cohort studies such as the Primary Retinal Detachment Outcomes (PRO) study suggest that a combination of PPV and SB (PPV-SB) has an advantage over PPV alone for phakic and pseudophakic patients [1, 2]. Similarly, a meta-analysis of cohort studies suggests that there may be an increased rate of surgical success without reoperation in patients receiving PPV-SB [3]. However, the few randomized controlled trials (RCT) with small sample sizes (range 30 to 100 patients per group) and heterogenous surgical techniques looking into this question have not found an advantage to additional SB [4–7], and a recent meta-analysis of RCT has also not found an advantage but rather increased myopization, duration of surgery, and postoperative pain following additional SB [8]. In a way to simulate randomization, we performed a propensity score analysis comparing the surgical outcomes of PPV compared to PPV-SB at our center which also showed similar results between both techniques [9]. The discrepancy between the results of non-randomized and randomized studies in this debate is likely due to indication bias, that is, the tendency of surgeons to treat more complex patients using PPV-SB thinking that it will provide them with a better outcome.

In addition to this choice of surgical technique, there is also the use of different gas tamponades which can be of interest. Most commonly, vitreoretinal surgeons use either sulfur hexafluoride gas (SF_6_) or perfluoropropane gas (C_3_F_8_) to maintain the reapproximation of the retina postoperatively, reserving the use of silicone oil to refractory cases where a longer tamponade is needed. SF_6_ remains in the eye for 2 to 3 weeks, while C_3_F_8_ remains in the eye for 6 to 8 weeks. There may therefore be an indication bias to use C_3_F_8_ in more complex cases where a longer tamponade duration is desired. Unfortunately, there are no RCT comparing these two tamponade agents, while studies comparing air and gas tamponades have had mixed results [10, 11].

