### Eligibility criteria {10}

Patients aged ≥ 18 years diagnosed with RRD will be considered for inclusion. Since very simple RRD are more likely to be treated with PPV, while more complex RRD are more likely to be treated with PPV-SB, we will select patients who have a moderately complex RRD, like the PRO study. This excludes the following characteristics: proliferative vitreoretinopathy (PVR) grade ≥ C2, chronic RRD with duration > 3 months, proliferative diabetic retinopathy with tractional retinal detachment (RD), macular holes, epiretinal membrane grade 3 or 4, traumatic RD, giant retinal tears, retinal dialysis, foveoschisis, wet age-related macular degeneration, endophthalmitis, acute retinal necrosis, Coats disease, retinopathy of prematurity, retinoschisis, retinal colobomas, prior glaucoma surgery or strabismus surgery (difficulty with adding SB), and superior RD extent less than 3 clock hours (favoring PPV).

Age younger than 45 years is a relative exclusion factor whereby, if the surgeon considers the patient more eligible for an SB-only procedure, they will not be considered for the study. In contrast to the PRO study, we will accept moderate degrees of PVR and RD extent greater than 9 clock hours (favoring PPV-SB). We also did not consider certain factors which were included given that the PRO study also included SB-only procedures (e.g., significant vitreous opacities, cataract, prior vitrectomy, greater than moderate vitreous hemorrhage).

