#### Strategies to improve adherence to interventions {11c}

The intervention allocation will be determined based on the preoperative appearance of the RRD and will not be permitted to change once in the operating room.

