### Assignment of interventions: blinding

#### Who will be blinded {17a}

Outcome assessors, investigators, and data analysts will be blinded to the assignment of the interventions and the attributed code in the database until the end. For feasibility reasons, the trial participants and the clinical team including the treating surgeon will not be blinded to the intervention allocation. Blinding of the treating surgeon in relation to surgery technique will not be possible given that they will be responsible for adding the SB, and this will be visible on dilated fundus examination at follow-up given the scleral depression caused by the SB, while blinding to gas tamponade will not be feasible given that the gas bubble will dissipate at a faster rate with SF_6_ compared to C_3_F_8_ on follow-up examinations. As for trial participants, they are operated under local anesthesia with a retrobulbar block and sedation. They can therefore overhear surgeons discussing the next steps with the scrub nurse, deduce the addition of the SB based on duration of surgery, and see the speed at which the gas disappears from their visual field. 

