#### Methods in analysis to handle protocol non-adherence and any statistical methods to handle missing data {20c}

Outcomes will be analyzed as randomized. Missing data will be handled using multiple imputation.

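### A surgeon who knows the allocation may remove a randomised patient judged to need silicone oil, which conflicts with analysis as randomised and could bias SSAS if removal differs by arm

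*Protocol article*

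**What the plan says.** Protocol article, Criteria for discontinuing or modifying allocated interventions {11b}, sets the trigger: "Should the patient require silicon oil as a tamponade agent as deemed by the treating surgeon upon starting the operation". Its one example is "in cases of extensive PVR undetected preoperatively", and its consequence is that "the patient could therefore be removed from the study and treated accordingly". No grade, criterion or independent confirmation is attached.

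Four other sections bear on this:

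- Implementation {16c} places randomisation at enrolment. Participant timeline {13} places surgery up to 48 hours (macula-on) or 5 days (macula-off) after allocation. The removal decision therefore follows randomisation.
- Who will be blinded {17a} states that "the trial participants and the clinical team including the treating surgeon will not be blinded to the intervention allocation".
- The section on non-adherence and missing data {20c} states "Outcomes will be analyzed as randomized", and adds that missing data will be multiply imputed.
- Background and rationale {6a} describes usual practice as "reserving the use of silicone oil to refractory cases where a longer tamponade is needed".

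**The concern.** Three features of the rule matter in combination. It acts after randomisation, it depends on the judgement of someone who knows the allocation, and it applies to eyes that are likely to fail. A patient who has left the study cannot also contribute an SSAS result in the allocated arms, so {11b} and {20c} do not fit together.

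The protocol supplies a mechanism for removal to differ by arm. Background and rationale {6a} attributes the disagreement between cohort studies and randomised trials to surgeons choosing PPV-SB for harder cases in the belief that it does better. It raises the same possibility for C3F8. A surgeon with those beliefs who meets a difficult eye allocated to PPV alone or to SF6 may be readier to turn to oil. Each such removal would take a probable failure out of that arm and raise its observed SSAS. The indication bias that randomisation was meant to exclude could then return, in both factorial comparisons.

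Multiple imputation would not repair this. If removed patients are outside the dataset, nothing is imputed for them. If they are imputed, the model learns from gas-treated eyes with a better outlook.

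**Working it through.** **The plan's own figure.** With effect size 0.25, two-sided alpha 0.05 (sidedness assumed) and 80% power, n per margin = 2(1.960 + 0.842)² / 0.25² ≈ 251.2, rounded up to 252. The total is 504, and 504 / 0.9 = 560. Both match Sample size {14}. Power at 252 per margin is 80.1%. Removing a further 1%, 2%, 3% or 5% lowers it to 79.7%, 79.3%, 78.9% or 78.1%. Loss of power is therefore minor, and the issue is bias.

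**Inputs for the bias.** The protocol gives neither an oil rate nor the outcome of oil-treated eyes, so both are assumptions here.

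**View 1: how much true difference removal would hide.** Let retained eyes fail at 10% in both arms, switched eyes fail at rate f, and the switch rates be rA and rB. Keeping everyone, an arm's failure rate is 0.10 + r(f − 0.10). After removal both arms show 10%. The hidden difference is therefore

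(rA − rB) × (f − 0.10).

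With rA between 2% and 5%, rB between 1% and 2%, and f between 40% and 60%:

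- smallest: (0.02 − 0.02) × (0.40 − 0.10) = 0 points
- largest: (0.05 − 0.01) × (0.60 − 0.10) = 2.0 points

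**View 2: how much spurious difference removal would create.** Now let as-randomised SSAS be 90% in both arms, with 280 per margin and no dropout. Let q be the SSAS of the removed eyes had they been kept. SSAS among retained eyes is (0.90 − r·q) / (1 − r). For 2% against 5% removed and q = 50%:

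- (0.90 − 0.010) / 0.98 = 90.8%
- (0.90 − 0.025) / 0.95 = 92.1%
- spurious difference 1.3 points

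| Removed, arm 1 / arm 2 | q = 70% | q = 50% | q = 30% |
|---|---|---|---|
| 2% / 2% | 0 | 0 | 0 |
| 5% / 5% | 0 | 0 | 0 |
| 2% / 5% | 0.6 points (type I error 5.8%) | 1.3 points (8.4%) | 1.9 points (13.4%) |
| 0% / 5% | 1.1 points (7.0%) | 2.1 points (13.9%) | 3.2 points (26.6%) |

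Equal removal gives no between-arm difference. It does raise observed SSAS in both arms, from 90% to between 90.4% (2% removed, q = 70%) and 93.2% (5% removed, q = 30%).

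**Scale.** The standard error of the SSAS difference at 90% and 280 per margin is √(2 × 0.9 × 0.1 / 280) = 2.5 points.

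**The case against.** The strongest defence is that the rule mostly catches ineligibility found late. Its example is a condition present before allocation, and Eligibility criteria {10} already excludes "proliferative vitreoretinopathy (PVR) grade ≥ C2". This stands in part: a rule tied to that baseline criterion and judged without knowledge of the arm would be much safer. But {11b} is not so tied. PVR is only an example, and the trigger is an unblinded judgement that oil is needed.

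A second defence is that removal is optional and that the participant retention section {18b} collects the reason, final visual acuity and retina status when a participant discontinues follow-up. That allows a reading in which these patients are still analysed as randomised. However, {18b} does not mention removal by the surgeon, and it does not name reoperation. An eye attached at the end after a second operation is an SSAS failure that final retina status would not show.

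A third is that the need for oil is judged as surgery starts, whereas gas goes in at the end. This does not exclude influence from the gas allocation, because nothing in the protocol withholds it from the surgeon until then.

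Two stronger readings should be resisted:

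- A reader might infer that the rule also contradicts {11c}, under which the allocation "will not be permitted to change once in the operating room". It does not. A removed patient receives neither allocated gas but is not reassigned, so the two sections can coexist.
- A reader might treat between-arm bias as established. The documents offer a plausible mechanism but no evidence that removal will differ by arm.

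**Conclusion.** The conflict between {11b} and {20c} is real and does not depend on any assumed figure. It is a stated rule against a stated rule, not a detail left to an analysis plan.

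The bias is conditional and its size unknown. Under switch rates of 2-5% against 1-2%, with 40-60% failure in switched eyes against 10% otherwise, it runs from 0 to 2.0 points. That is at most about one standard error, and small beside the 10-point difference that Outcomes {12} calls clinically relevant. It would not by itself invalidate the trial. Even so, the more unequal cases in the table push type I error well above 5%. If removal is commoner under PPV or SF6, SSAS in those arms is flattered; if it is equal, SSAS is inflated throughout and the results describe a narrower population.

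**What to change.** Reconcile {11b} with {20c}. Leave the choice of treatment to the surgeon, as now, and replace removal from the study with wording to this effect: the patient stays in follow-up to 12 months, is analysed in the allocated technique and gas arms for SSAS and all other outcomes, and has the oil use recorded as a deviation. Any analysis without these eyes should be a labelled sensitivity analysis.

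A sentence confirming that planned oil removal is not an SSAS failure would help. It is clarification only, because Outcomes {12} already limits failure to reoperation for recurrent RRD.

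The cost is an amendment to wording and follow-up of a few more patients at the single centre. Keeping oil-treated eyes in the arms slightly dilutes the technique and gas contrasts. Trial status gives recruitment running to about July 2027. The change is best made early, because outcomes of patients already removed may not be recoverable.

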#### Strategies to improve adherence to interventions {11c}

The intervention allocation will be determined based on the preoperative appearance of the RRD and will not be permitted to change once in the operating room.

#### Relevant concomitant care permitted or prohibited during the trial {11d}

Any concomitant care required by the patient’s ophthalmological condition will be permitted during the trial, including other medical treatments or surgical procedures.

#### Provisions for post-trial care {30}

After the 1-year follow-up included as part of the trial, if there are still ongoing retinal or other ophthalmological conditions which require active subspecialty management, patients will continue to be followed by the retina or ophthalmology team of the CHU de Québec – Université Laval indefinitely or until resolution of said conditions. If there are no ongoing retinal or other ophthalmological conditions, standard eyecare follow-up could be performed by community optometrists.

### Outcomes {12}

The primary outcome is SSAS defined as freedom from reoperation for recurrent RRD at all follow-up evaluations. Localized recurrences or new tears treated using a laser in the ambulatory clinic will not be considered a failure of the primary surgery but will be noted. We considered a difference of 10% in SSAS to be clinically relevant for this trial and based the sample size calculation on this threshold of chosen efficacy. Secondary outcomes will include PHVA at 8–10 weeks and 6 months, final BCVA, final retina status (i.e., attached or detached), time to onset of RD recurrence, severity and number of complications, and questionnaire results (see Additional file 1). The principal questionnaire was previously used and validated by Potic et al. [12] with additional questions used to specifically assess possible side effects and reductions in quality-of-life associated with the addition of SB and longer-duration intraocular gases. In cases of primary surgery failure, the cause of recurrence (i.e., PVR including epiretinal membrane (ERM) in the macular area causing recurrent RD, new or recurrent retinal breaks) will be reviewed. The extent of PVR at follow-up will also be evaluated. The duration of surgery will also be collected. Number of additional visits and supplementary laser and intraocular pressure treatments will be evaluated. Complications will be graded using the novel Classification of Ophthalmological Complications (COC; see Table 1).

**Table 1 Tab1:** Classification of ophthalmological complications (COC)

Complication grade	Definition
Grade I	Any deviation from the normal postoperative course without the need for modification of planned pharmacological treatment or surgical intervention Allowed therapeutic regimens are as follows: any previous medication, any medication prescribed routinely (i.e., topical antibiotics, glaucoma drops, anti-inflammatory drops, steroid drops, oral pills), artificial tears, hot compresses, and analgesic drugs (Advil/Tylenol only)
Grade II	Requiring change in planned pharmacological treatment with higher frequency or longer duration of drops or the introduction of new drugs (including autologous serum drops); these can include glaucoma drops and steroid drops and the use of oral drugs other than Advil/Tylenol (e.g., Diamox, prednisone). Also includes YAG capsulotomy
Grade III	Requiring any laser procedures other than YAG capsulotomy or any periocular/intraocular injections. Simple interventions performed at the slit lamp (e.g., AC burp or tap, AC filling, epithelial debridement) or under local anesthesia not requiring an OR setup (e.g., pneumatic retinopexy, keratectomy, leaking wound requiring additional suture) are also included
Grade IV	Requiring intervention with an OR setup or requiring pharmacological treatment with intravenous drugs or hospitalization
Grade V	Sight-threatening complication or loss of eye (endophthalmitis, globe rupture, suprachoroidal hemorrhage)
Grade Va	Unilateral sight-threatening complication or loss of eye (endophthalmitis)
Grade Vb	Bilateral sight-threatening complication or loss of eyes (bilateral endophthalmitis, bilateral eye trauma, sympathetic ophthalmia)
Grade VI	Life-threatening complications (including CNS complications) requiring IC/ICU management
Grade VII	Death

### Participant timeline {13}

Table 2 illustrates the patient timeline for the study. Preoperative baseline characteristics will include age, sex, symptoms duration, pinhole visual acuity (PHVA) at presentation in metric Snellen notation defined as the best visual acuity obtained using the patient’s current refraction with or without improvement with pinhole, laterality of presentation, myopia greater than four diopters, lens status (i.e., aphakic: patient without their native crystalline lens or an intraocular lens; phakic: patient with their native crystalline lens; pseudophakic: patient with an intraocular lens replacing their native crystalline lens), macula status (i.e., on, off, split), RD extent in clock hours, number of retinal breaks assessed preoperatively and under direct intraoperative visualization, and inferior retinal breaks in the detached retina between 4:00 and 8:00 clock hours. Patients will be assessed at 1 day postoperatively, 2 weeks, 8–10 weeks, 6 months, and 12 months and any additional follow-ups as needed on an emergent basis. At each scheduled follow-up, visual acuity will be assessed using a Snellen visual chart with pinhole and intraocular pressure measured by Goldmann applanation, iCare, Accupen, and Tonopen. LOCS III grading for cataract development will be used to evaluate patients’ lens at each follow-up. Multimodal imaging using macular optical coherence tomography (OCT), optic nerve/retinal nerve fiber layer (RNFL) OCT, ganglion cell layer (GCL) OCT measures, OCT angiography, widefield fundus photography, and fundus autofluorescence will be conducted when it is possible (after gas disappearance at 6 months and 12 months). Starting at the 8–10-week follow-up, autorefraction will be used. Quality of life questionnaires will also be administered to patients at each follow-up starting at the 2-week postoperative follow-up.

**Table 2 Tab2:**
[figure not shown]
Schedule of enrollment, interventions, and assessments in the REDOS trial

^1^Age, sex, symptoms duration, and pinhole visual acuity (PHVA) at presentation in metric Snellen notation defined as the best visual acuity obtained using the patient’s current refraction with or without improvement with pinhole, laterality of presentation, myopia greater than 4 diopters, lens status (i.e., aphakic, phakic, pseudophakic), macula status (i.e., on, off, split), RD extent in clock hours, number of retinal breaks assessed preoperatively and under direct intraoperative visualization, and inferior retinal breaks in the detached retina between 4:00 and 8:00 clock hours

^2^PHVA intraocular pressure measured by Goldmann applanation, iCare, Accupen, and Tonopen; LOCS III grading for cataract development; retina status (i.e., attached or detached)

^3^Multimodal imaging using macular optical coherence tomography (OCT), optic nerve/retinal nerve fiber layer (RNFL) OCT, ganglion cell layer (GCL) OCT measures, OCT angiography, widefield fundus photography, and fundus autofluorescence will be conducted when it is possible (e.g., after gas disappearance at 6 months and 12 months). Starting at the 8–10-week follow-up, autorefraction will be used

^4^See Additional file 1

The 2-week follow-up examination could be performed on select patients outside of the study center. These include patients from remote regions outside Quebec City and those from regions prohibiting travel to the study center with intraocular gas tamponade (e.g., through mountainous or high-altitude regions). In those cases, the postoperative questionnaire would be answered with a research team member by phone.

Patients with macula-on RRD will be operated on within 48 h of preoperative assessment and allocation, while patients with macula-off RRD will be operated on within 5 days of preoperative assessment and allocation.

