#### Intervention description {11a}

Surgery will be performed under local anesthesia with retrobulbar block (5 to 10 cc of 2% lidocaine without epinephrine and 0.5% bupivacaine in a 1:1 ratio). In all cases, surgery will be performed using a wide-angle viewing system and the Alcon Constellation System (Alcon Laboratories, Inc., Fort Worth, TX) combined with the ULTRAVIT 23-G + or 25-G + vitreous cutter (Alcon).

Pars plana vitrectomy will be performed in a standard fashion starting with central vitrectomy, then by localizing retinal breaks and marking them with endodiathermy. Perfluorocarbon will be used to displace subretinal fluid which will be aspirated at its exit from the retinal break as much as possible to avoid retinal pigment epithelium (RPE) dispersion into the vitreous and maximal vitreous base shaving will be performed in all cases. This will be followed by an air-fluid exchange. The use of cryotherapy to solidify the retina intraoperatively and the use of internal limiting membrane peeling of the posterior pole will be at the discretion of the surgeon. In all cases, laser photocoagulation around retinal breaks, holes, areas of lattice degeneration, and posterior to sclerotomy sites will be done and then a 360° laser retinopexy will be performed at the surgeon’s discretion and consisted of three rows of medium-white burns anterior to the level of the vortex vein, towards and beyond the equator. In cases with SB, after 360° peritomy and dissection in 4 quadrants, a 41-circling band with 3082 sleeves (Labtician Ophthalmics, Oakville, ON, Canada) will be used in all cases and fixed to the sclera at approximately 11.5 mm from the limbus (or 5.5 from the insertion of rectus muscles) using partial thickness scleral tunnel or mattress sutures with 5.0 prolene or nylon performed in four quadrants depending on the surgeon preferences. At the end of the surgery, a gas tamponade will be injected inside the eye, either SF_6_ or C_3_F_8_. The surgical technique at the second surgery, if applicable, will be at the discretion of the treating surgeon.

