### Assignment of interventions: allocation

#### Sequence generation {16a}

Given the large sample size that we aim to achieve, patients will be randomized using simple randomization with computer-generated random numbers at the time of enrollment. A sequence will therefore not be generated in advance. No stratification will be used given that the goal is to allow for the generalizability of the results to any patient presenting with moderately complex RRD.

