#### Implementation {16c}

The simple randomization will be done at the time of enrollment by the research assistant who will obtain the signed patient consent.

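### The gas is randomised at enrolment with no deferred disclosure to an unblinded surgeon, so discretionary operative steps can follow the gas assignment

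*Protocol article*

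**What the plan says.** **Timing of allocation.** Under Sequence generation {16a}, "patients will be randomized using simple randomization with computer-generated random numbers at the time of enrollment". Implementation {16c} gives the task to one person: "The simple randomization will be done at the time of enrollment by the research assistant who will obtain the signed patient consent". Neither section separates the two factors. The text below Table 2 in Participant timeline {13} sets the longest interval to surgery for one group: "patients with macula-off RRD will be operated on within 5 days of preoperative assessment and allocation". The limit for macula-on eyes is 48 h. Strategies to improve adherence {11c} adds that the allocation "will not be permitted to change once in the operating room".

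**Timing of use.** Intervention description {11a} places the gas last: "At the end of the surgery, a gas tamponade will be injected inside the eye, either SF_6_ or C_3_F_8". Among the steps before it, "the use of internal limiting membrane peeling of the posterior pole will be at the discretion of the surgeon"; the same sentence leaves cryotherapy to the surgeon, and a later one does so for the 360° laser.

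**Blinding.** Who will be blinded {17a} leaves participants and the clinical team, including the treating surgeon, unblinded. For technique, the reasons are that the surgeon places the buckle and that it is visible at follow-up. For gas, the reason is that "blinding to gas tamponade will not be feasible given that the gas bubble will dissipate at a faster rate" with SF6 than with C3F8 when the eye is examined at follow-up.

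**The concern.** The two factors differ in when the surgeon needs to know them. The technique must be known before or during the operation. The gas need not be known until it is injected, and the reason given in {17a} for not blinding the surgeon to it begins to apply only after that. The protocol thus leaves a period, the operation itself, in which the surgeon may know the gas without any stated need to.

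This matters because some of what happens in that period is discretionary. The Background notes a possible tendency to choose C3F8 for more complex eyes where longer tamponade is wanted. A surgeon with that view, knowing that an eye will receive SF6, could use the optional steps more readily. The gas groups would then differ in operative treatment as well as in gas. The Discussion asks whether the longer-acting gas is necessary, and a difference in SSAS, or its absence, would be harder to attribute to the gas alone. At stake is the gas comparison, which Objectives {7} names as secondary. The technique comparison is not affected by this point.

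**Working it through.** **Step 1. Sequence of events as written.**

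| Event | Technique | Gas | Source |
|---|---|---|---|
| Assignment drawn | Enrolment | Enrolment | {16a}, {16c} |
| Interval to surgery | Up to 48 h (macula-on) or 5 days (macula-off) | Same | {13} |
| Assignment first acted on | During surgery, when the buckle is placed or omitted | End of surgery | {11a} |
| Reason the surgeon is not blinded during surgery | Surgeon places the buckle | None given | {17a} |
| Reason the surgeon is not blinded after surgery | Buckle visible at examination | Bubble clears at different rates | {17a} |

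The gap is the fourth row, for gas.

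**Step 2. What can vary in the gap.** {11a} fixes maximal vitreous base shaving and laser around breaks, holes, lattice and behind the sclerotomies in all cases. Cryotherapy, internal limiting membrane peeling and the 360° laser are optional. The route for bias runs through these three, not through the whole operation.

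**Step 3. Can the size be derived?** No. The documents do not give the frequency of the optional steps, their effect on SSAS, or any difference in their use between gases. What follows is an illustration on assumed inputs.

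- Overall failure rate B: 10% to 13%. This agrees with Sample size {14}. In the centre's own phakic patients failure is 8% and 12%, mean 10%; in the phakic patients of the large retrospective cohort it is 17% and 9%, mean 13%.
- Relative reduction in failure from optional retinopexy, f: 0.25 to 0.50 (assumed).
- Average use: 60% (assumed). Gap in use between SF6 and C3F8, g: 0 to 40 points (assumed).

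Failure without the optional step is F0 = B / (1 − 0.6f). Failure in an arm with use u is F0 × (1 − f × u). The difference due only to unequal use is therefore F0 × f × g.

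| B | f | F0 | g = 0 | g = 0.10 | g = 0.20 | g = 0.40 |
|---|---|---|---|---|---|---|
| 0.10 | 0.25 | 0.10/0.85 = 0.1176 | 0 | 0.3 points | 0.6 points | 1.2 points |
| 0.13 | 0.50 | 0.13/0.70 = 0.1857 | 0 | 0.9 points | 1.9 points | 3.7 points |

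For comparison, Outcomes {12} treats 10 points as clinically relevant, and the cohort differences cited in {14} are 8 points (91 − 83 and 92 − 84).

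**Step 4. Direction.** If extra treatment went to SF6 eyes and worked, SF6 would look better than it is. Were C3F8 truly better, that would shrink the difference; were the gases equal, it would create one. The documents do not settle which case applies, or whether the optional steps would be used unequally at all.

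**Step 5. Effect of the remedy on the design.** Later release of the gas assignment changes neither the draws nor the analysis. The planned 560 × 0.9 = 504 evaluable patients, the 0.05 level and the power are unchanged.

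**The case against.** Four arguments stand against the point.

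*The time of disclosure is not stated.* The protocol says when the assignment is drawn, not when the surgeon is told. A reader might infer that the surgeon knows the gas up to five days ahead, but no section says so, and five days is the maximum for macula-off eyes only. This stands. What remains is that a draw at enrolment, an unblinded surgeon and no described deferral leave such knowledge possible.

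*The core operation is standardised.* A reader might infer that every operative step is exposed. {11a} does not support that, and nothing in it suggests that surgeons vary the optional steps by gas. This also stands and narrows the point to three steps.

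*Adjusting the operation to the gas may be part of the strategy compared.* The comparator section describes a choice that surgeons now make by preference, and {16a} stresses generalisability. This does not carry: the protocol states no such strategy estimand, and the question in its Discussion concerns the longer-acting gas itself.

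*Later release gains little.* SSAS is freedom from reoperation, and the treating team remains unblinded through 12 months. Correct: the change closes one route for bias and leaves the follow-up route open.

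**Conclusion.** The point holds as a cheap improvement to a secondary comparison. The reason given for leaving the surgeon unblinded to gas does not cover the operation, and three discretionary steps precede the injection. They can follow the gas assignment and bias the SF6 versus C3F8 result.

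The size cannot be determined from the documents. The illustration runs from 0 to 3.7 points in SSAS and rests on assumed use and benefit of the optional steps. A reader might infer a bias of several points, or one that pushes the gases towards appearing similar; the documents support neither. Nor do they support delaying release of the technique assignment, since the problem described is specific to gas.

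The conclusion rests on one inference: that the surgeon may learn the gas before injection, because no section provides otherwise.

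**What to change.** In {16a} and {16c}, keep both 1:1 draws at enrolment and leave release of the technique assignment as it is. Add that the database releases the gas assignment to operating room staff only after the surgeon declares all discretionary steps complete. In {17a}, state that the surgeon is blind to gas until that moment, and confine the bubble-dissipation reason to the period after it. The ban in {11c} on changing the allocation can stay, because the assignment is fixed at enrolment whether or not it has been shown.

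The cost is a database setting and a few sentences of protocol text. Both gases must be at hand for each operation, and patients must be counselled for either. Sample size, analysis and clinical rules are unchanged. Follow-up examinations and decisions to reoperate remain unblinded.
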